## Materials and methods

### Study design and setting

The S3E study adopts a mixed-methods design where a mix of qualitative and quantitative data collection techniques will be applied to investigate experiences of PLHIV concerning disrupted access to healthcare, treatment adherence, and coping mechanisms in addition to economic losses (including productivity losses) during the recent floods in South Africa. A retrospective community-based exposed-unexposed approach will be carried out in relation to the first two study objectives.

The study will be implemented in the Hlabisa municipality, where the Africa Health Research Institute (AHRI) hosting the study is located, and the Ndwedwe municipality, iLembe district, both in KZN, South Africa. Fig 1 represents the map of the two study areas. These two municipalities were selected because Hlabisa (i.e., unexposed group) was relatively spared by the floods, whilst Ndwedwe, iLembe (i.e., exposed group) was the second most affected sub-district after the city of Durban. The two sub-districts have been selected for comparison as they have similar sociodemographic profiles; both areas are under-resourced rural and socio-economically disadvantaged, and most people live below the poverty line [39,40]. In both areas, HIV is the leading cause of death in individuals aged 25–64 years [41], and antenatal HIV prevalence exceeds 40% [42].

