### Overview of participant recruitment and inclusion criteria

We will recruit PLHIV in the Hlabisa subdistrict through a randomisation process. Potential participants will be randomly drawn from – and recruited – through the AHRI Health and Demographic Surveillance System (HDSS) [39]. In this programme, triannual household-based surveys are used to collect sociodemographic data from approximately 150,000 people in an 845km^2^ area coupled with annual home-based, point-of-care HIV testing, linked to real-time HIV clinical data and health service utilisation records from all 11 regional primary healthcare clinics that provide HIV care, hospitalisation data at the single district referral hospital, and annually death data carried out through verbal autopsies of all deaths in the catchment area. This research database will be used as a sampling frame to randomly select and invite PLHIV to take part in the study in Hlabisa.

AHRI does not have a similar research infrastructure in Ndwedwe, iLembe district. To identify PLHIV in the community without stigmatising them, we will hold monthly meetings with the community engagement department (CED) at AHRI to engage the health facilities and traditional structures in Ndwedwe as part of the community entry process, trust building and stakeholder engagement. Part of this process will entail a series of road shows and edutainment programmes – led by the CED – encapsulating games and educational talks on climate change and health to sensitise the community about the study. Subsequently, the study team will work closely with community caregivers and community-based organisations who have access to PLHIV to facilitate recruitment. Individuals who are recruited through this process will be informed about the study and offered participation if they meet the eligibility criteria. Although it is logistically easier to recruit PLHIV from healthcare facilities, this will introduce selection bias as it means only PLHIV who are still able to access healthcare facilities will be offered participation in the study, and these individuals may differ from the general population of PLHIV in Ndwedwe.

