Participants will be recruited if (a) they are aged 18 years and over, (b) they were diagnosed with HIV before the April 2022 floods, (c) were on antiretroviral therapy before April 2022, (d) were resident in Ndwedwe (exposed group) or Hlabisa (unexposed group) over a month before and during April 2022, (e) were present for and remember the April 2022 floods (for the exposed group), and (f) they are able to give written consent.

More detailed data regarding the study participants and sample size for each study objective is provided in the following sections.

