#### Objective 2. Measuring the economic losses and healthcare related costs.

The background loss from care after 12 months of antiretroviral treatment ranges from 20–30% [51]. Therefore, we will need to recruit a total of 424 PLHIV (212 unexposed and 212 exposed individuals) at a matched exposed-unexposed ratio of 1:1 (one unexposed for one exposed) to reach an 80% power at 0.05 significance level to detect a 90% increase in odds of loss from care during the first 6 months following the floods. Although we do not aim to estimate loss from care (i.e., loss from follow-up) in this study, it underpins our study hypothesis while not the primary reason for this study. The AHRI HDSS databases described in the participant recruitment section will serve as the sampling frame for randomly selecting the 212 unexposed individuals in Hlabisa, of whom 70% will be female, which is representative of the proportion of females amongst all PLHIV who engage with the surveillance programme. A similar approach will be taken to recruit 212 exposed PLHIV in Ndwedwe by working closely with AHRI CED, community caregivers and other community-based organisations, as mentioned above.

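### Physical presence during the April 2022 floods is required of the exposed group only, so Hlabisa residents who were in a flooded area can be counted as unexposed and the two groups are screened differently on absence

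*Protocol article*

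**What the plan says.** Exposure is assigned by municipality. Under Study design and setting, "Hlabisa (i.e., unexposed group) was relatively spared by the floods", while Ndwedwe "was the second most affected sub-district after the city of Durban".

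Under Overview of participant recruitment and inclusion criteria, two conditions concern where people were:

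- Criterion (d), for both groups: they "were resident in Ndwedwe (exposed group) or Hlabisa (unexposed group) over a month before and during April 2022".
- Criterion (e), for one group only: they "were present for and remember the April 2022 floods (for the exposed group".

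Hlabisa participants are drawn at random from the surveillance database: "This research database will be used as a sampling frame to randomly select and invite PLHIV to take part in the study in Hlabisa". Ndwedwe participants are reached through community caregivers and community-based organisations. No criterion excludes a Hlabisa resident who met the floods somewhere else.

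**The concern.** In a retrospective exposed-unexposed comparison, the unexposed group has to be free of the exposure, and both groups should pass through the same filter on anything related to the outcome. The criteria fall short on both counts.

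1. **Misclassification.** Flood losses that a Hlabisa resident suffered elsewhere enter the unexposed mean and dilute the contrast.
2. **Differential selection.** People who were away from the floods are dropped from Ndwedwe and retained in Hlabisa. If absence was often for work, which is an assumption, the groups will differ in employment and earnings. Under the human capital approach in Data analysis, Objective 2, productivity loss depends on both. The direction of this second bias cannot be settled from the document.

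**Working it through.** **Step 1: the two criteria side by side.**

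| Condition in April 2022 | Ndwedwe (exposed) | Hlabisa (unexposed) |
|---|---|---|
| Resident, criterion (d) | required | required |
| Present for the floods, criterion (e) | required | not required |
| Remembers the floods, criterion (e) | required | not required |
| Not in a flooded area elsewhere | not applicable | not required |

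If residence under (d) already meant physical presence, the presence half of (e) would add nothing. By including it, the article treats residence and presence as separate conditions and then checks presence at one site only.

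**Step 2: who is affected.**

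- Hlabisa resident in Durban: meets (d) if still counted as resident, faces no further check, enters as unexposed.
- Hlabisa resident away in an unaffected place: kept.
- Ndwedwe resident away from any flooded area: fails (e), removed.
- Ndwedwe resident in another flooded area: may still meet (e), which does not say where the person had to be present.

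**Step 3: dilution of a mean difference.** Let m0 and m1 be the mean losses without and with exposure, and c the share of the unexposed group carrying the full exposed loss. The unexposed mean becomes (1 − c)·m0 + c·m1, so

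observed difference = m1 − [(1 − c)·m0 + c·m1] = (1 − c)·(m1 − m0).

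The contrast shrinks by exactly c: 5% at c = 0.05, 15% at c = 0.15. The article gives no value for c.

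**Step 4: the same dilution on the article's planning figures.** Inputs from Sample size, Objective 2: 212 per group, the stated effect ("detect a 90% increase in odds of loss from care during the first 6 months following the floods", so an odds ratio of 1.9), and the stated operating characteristics ("to reach an 80% power at 0.05 significance level"; two-sided is my assumption). The background is stated as a range: "The background loss from care after 12 months of antiretroviral treatment ranges from 20–30" per cent.

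First, the plan's own figure. With p0 = 0.20, p1 = 1.9 × 0.20 / (0.80 + 1.9 × 0.20) = 0.38 / 1.18 = 0.322. The log-odds formula gives

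n = (1.960 + 0.842)² × [1/(0.20 × 0.80) + 1/(0.322 × 0.678)] / (ln 1.9)² ≈ 7.849 × 10.83 / 0.412, which rounds up to 207 per group.

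The pooled two-proportion formula gives 203, and a McNemar calculation with no within-pair correlation gives 205. Power at 212 per group is 0.8185 by the pooled formula. The stated 212 is therefore reproduced closely at the 20% end of the range. At p0 = 0.30, the pooled formula needs only 165 per group, and power at 212 is 0.889.

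Now let a share c of the unexposed group have risk p1, so the unexposed risk is (1 − c)·p0 + c·p1. At c = 0.05 and p0 = 0.20 this is 0.2061, and the observed odds ratio is 0.475 / (0.2061/0.7939) = 1.83.

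| c (assumed) | OR, p0 = 0.20 | Power, p0 = 0.20 | OR, p0 = 0.30 | Power, p0 = 0.30 |
|---|---|---|---|---|
| 0 | 1.90 | 0.819 | 1.90 | 0.889 |
| 0.02 | 1.87 | 0.802 | 1.87 | 0.876 |
| 0.05 | 1.83 | 0.775 | 1.83 | 0.854 |
| 0.10 | 1.76 | 0.726 | 1.77 | 0.812 |
| 0.20 | 1.64 | 0.617 | 1.66 | 0.712 |

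The article says loss from care is not something the study aims to estimate, so this table only illustrates scale. Step 3 is the part that carries over to cost and productivity outcomes.

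**The case against.** The best defence is that (d) already does the work. A residence window that is short and tied to the event reads naturally as living there at the time, so someone staying in Durban that month was not a Hlabisa resident. Criterion (e) may be no more than a joint check that exposed participants experienced the floods and can report on them, and it could not be applied word for word to an area that was largely spared. How residence is verified is also detail that an article may leave to the full protocol. This does not remove the point: the one-sided presence condition is a stated rule, not an omitted detail, and the lenient reading of (d) leaves half of (e) redundant. The defence does justify keeping the recall condition for the exposed group alone.

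Three other counterpoints stand in part.

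- **Exposure is set at community level**, so some individual movement is inherent in the design. That limits how serious the point is.
- **The size is easily overstated.** A Hlabisa resident caught in Durban still had a home and clinic in the spared area, so giving that person the full exposed loss is close to a worst case. At c = 0.02 the effect is negligible.
- **Some mitigation exists.** Employment status is collected and the model adjusts for baseline covariates, which could ease the selection problem but not the misclassification. The Objective 1 interviews in the unexposed area ask about other floods, and their findings feed into the Objective 2 questionnaire. That is a route to a location question, not a guarantee of one.

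A reader might infer that a Ndwedwe resident who was in Durban is excluded while the Hlabisa counterpart is kept. The text does not support that, because (e) names the floods and not the municipality. A reader might also take 10% absence for work at each site and conclude that 21 of 212 unexposed participants (0.10 × 212 ≈ 21) but none of the exposed would be such workers. The article supplies no absence rate, and the zero fails for anyone who was away in another flooded area.

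**Conclusion.** The concern holds in a limited form. Presence is required on one side of the comparison and not on the other. As written, this lets people who met the floods elsewhere into the unexposed group, and it removes those away from any flooded area from the exposed group only.

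The size is unknown. The dilution equals c only if the affected Hlabisa participants carried the full exposed loss, which is near an upper bound, and no value of c can be taken from the article. The bias may be small. This is a cheap improvement and not a flaw that undermines the study.

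**What to change.** - Apply one presence rule to both groups: physically present in the municipality of residence during the April 2022 floods.
- Keep the recall condition for the exposed group only.
- Record every participant's location in April 2022 with one screening question.
- Add a sensitivity analysis that excludes unexposed participants who were in a flood-affected area.

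Relaxing the rule to residence alone at both sites would also be symmetric, but it would admit Ndwedwe residents who never experienced the floods and would leave the misclassification in Hlabisa untouched. It is not recommended.

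The cost is one added question, a short amendment, and a few Hlabisa invitees and Ndwedwe volunteers screened out and replaced. Hlabisa replacements can come from the surveillance frame. Data collection, Objective 2 says the questionnaire is still to be finalised and piloted after the preliminary qualitative analysis, so the question can be added before fieldwork. Location that is not asked about at interview would be hard to recover later.

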### Sample size

#### Objective 1. Understanding the impacts of recent floods.

Under objective 1, we will recruit a minimum of 30 participants (PLHIV) for the IDIs across the exposed and unexposed sites: about 15 participants per site to provide in-depth reflections on the floods and its impacts. We will also organise two FDGs – one in each site – consisting of about six to eight participants per group. We will aim to achieve age and gender balance in the selection of participants while taking into consideration the context-specific issues in each study site. Finally, we will recruit about ten key informants comprising policymakers from health, disaster management, social welfare and housing for the interview through the personal and professional networks of the research team. The actual number of IDIs and KIIs to be undertaken will depend on data saturation.

#### Objective 2. Measuring the economic losses and healthcare related costs.

The background loss from care after 12 months of antiretroviral treatment ranges from 20–30% [51]. Therefore, we will need to recruit a total of 424 PLHIV (212 unexposed and 212 exposed individuals) at a matched exposed-unexposed ratio of 1:1 (one unexposed for one exposed) to reach an 80% power at 0.05 significance level to detect a 90% increase in odds of loss from care during the first 6 months following the floods. Although we do not aim to estimate loss from care (i.e., loss from follow-up) in this study, it underpins our study hypothesis while not the primary reason for this study. The AHRI HDSS databases described in the participant recruitment section will serve as the sampling frame for randomly selecting the 212 unexposed individuals in Hlabisa, of whom 70% will be female, which is representative of the proportion of females amongst all PLHIV who engage with the surveillance programme. A similar approach will be taken to recruit 212 exposed PLHIV in Ndwedwe by working closely with AHRI CED, community caregivers and other community-based organisations, as mentioned above.

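### The 80% power for Objective 2 pairs a 12-month background rate with a 6-month outcome; on an assumed constant hazard, 212 per group gives about 62–77% (two-sided, unmatched)

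*Protocol article*

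**What the plan says.** All the sizing inputs stand in the Sample size section, under Objective 2 (measuring economic losses and healthcare-related costs):

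- Background rate: "The background loss from care after 12 months of antiretroviral treatment ranges from 20–30" per cent.
- Size: the next sentence opens with an inference from that rate and arrives at "a total of 424 PLHIV (212 unexposed and 212 exposed individuals"), "at a matched exposed-unexposed ratio of 1:1 (one unexposed for one exposed").
- Operating characteristics: "to reach an 80% power at 0.05 significance level". Sidedness is not stated.
- Effect and window: "to detect a 90% increase in odds of loss from care during the first 6 months following the floods", that is, an odds ratio of 1.9 over 6 months.
- Role of the outcome: "Although we do not aim to estimate loss from care (i.e., loss from follow-up) in this study". The same sentence adds that it underpins the study hypothesis.

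The section does not say which value within 20–30% was used, what the 6-month background is, or what within-pair correlation the matching is expected to give. The inclusion criteria require only that participants "were on antiretroviral therapy before April 2022", with no limit on time since starting treatment.

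**The concern.** Power for an odds ratio depends strongly on the event rate in the unexposed group. The article presents 212 per group as following from a rate accumulated over 12 months, yet the outcome being powered accumulates over 6. Unless nearly all of the year's loss falls within six months, the 6-month rate is lower, fewer events are expected, and power at a fixed odds ratio falls.

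What is at stake is whether the sizing statement follows from its own inputs. It is the only quantitative basis given for enrolling 424 people in Objective 2, and a reader will take the 80% at face value.

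**Working it through.** **Inputs from the article.** Odds ratio 1.9; 212 per group, 1:1; power 80%; level 0.05; background 20–30% at 12 months.

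**Assumptions added here.** Two-sided test; unmatched pooled two-proportion formula unless stated otherwise; constant hazard for the conversion to 6 months.

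**Formulas.**
- Exposed rate: p1 = 1.9·o/(1 + 1.9·o), with o = p0/(1 − p0).
- Size per group: n = [1.960·√(2p̄(1 − p̄)) + 0.842·√(p0(1 − p0) + p1(1 − p1))]² / (p1 − p0)², with p̄ = (p0 + p1)/2. Power at 212 comes from solving the same expression for the power term.

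**Step 1: reproduce 212 from the 12-month rate, unconverted.**

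| p0 | p1 | n per group | n, continuity-corrected | power at 212 |
|---|---|---|---|---|
| 20% | 32.2% | 203 | 219 | 81.8% |
| 21% | 33.6% | 197 | 212 | 83.0% |
| 25% | 38.8% | 179 | 193 | 86.3% |
| 30% | 44.9% | 165 | 179 | 88.9% |

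A Wald test on the log odds ratio at 20% needs 207 per group. The stated 212 therefore sits comfortably with the low end of the 12-month range used as it stands.

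**Step 2: convert to 6 months.** Under a constant hazard, p6 = 1 − √(1 − p12).

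| 12-month rate | 6-month p0 | p1 at OR 1.9 | power at 212 | n per group for 80% | OR detectable with 80% at 212 |
|---|---|---|---|---|---|
| 20% | 10.6% | 18.3% | 62.4% | 321 | 2.17 |
| 25% | 13.4% | 22.7% | 70.5% | 267 | 2.04 |
| 30% | 16.3% | 27.1% | 76.6% | 231 | 1.95 |

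Simple halving instead (10%, 12.5%, 15%) gives power of 60.5%, 68.2% and 74.1%.

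**Step 3: break-even.** Power at 212 reaches 80% when the 6-month background is 18.5%. As a share of the 12-month loss that is 18.5/20 = 93%, 18.5/25 = 74% or 18.5/30 = 62%.

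**Step 4: allow for matching.** McNemar power with 212 pairs at the converted rates, with φ the within-pair correlation of the outcome:

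| 12-month rate | φ = 0 | φ = 0.1 | φ = 0.2 | φ = 0.3 |
|---|---|---|---|---|
| 20% | 61.9% | 66.3% | 71.2% | 76.6% |
| 25% | 70.0% | 74.3% | 79.0% | 83.9% |
| 30% | 76.1% | 80.2% | 84.4% | 88.7% |

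Matching restores 80% at φ of about 0.1 if the 12-month rate is 30%, but needs φ above 0.3 if it is 20%.

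**Step 5: does 212 prove that no conversion was made?** No. With 25% converted to 13.4% and a one-sided 0.05 test, about 210 per group are needed unmatched, or 212 pairs at φ = 0. With 30% converted to 16.3%, two-sided and matched at φ = 0.1, about 211 pairs are needed.

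**The case against.** Four arguments on the other side have weight.

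1. **The size does not identify the method.** Step 5 shows that converted 6-month rates can also lead to about 212, through a one-sided test or a modest pair correlation. This stands. A reader might infer that the authors must have used the 12-month rate unconverted, or that 212 is reachable only at 20–21%; the article supports neither. It shows only that the stated inputs do not lead to the stated power without an assumption it omits.

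2. **The shortfall is conditional.** The article gives no 6-month rate and no hazard shape, and it specifies matching. This also stands: 62–77% is not a property of the design but the result of a constant hazard with an unmatched two-sided test. Front-loaded loss could close the gap. However, eligibility is not limited to people newly on treatment, so the six months after the floods are not in general the first six months of therapy, and the article gives no ground for assuming early loss in that window.

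3. **The 12-month figure may not describe this population.** It is tied to duration of treatment, while participants may have been treated for any length of time. That is a fair caution about any conversion, and equally about using the figure unconverted.

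4. **Loss from care will not be estimated.** A reader might infer that a null result on loss from care would be misread as excluding an effect, or that the cost and productivity comparisons are underpowered. Neither follows. No loss-from-care estimate is planned, and this calculation says nothing about precision for the economic outcomes. It limits the consequence but does not make the power sentence correct.

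**Conclusion.** The mismatch of time frames is real and is visible in two consecutive sentences. The stated 80% does not follow from the inputs given. It needs a 6-month background of at least about 18.5%, a useful pair correlation, or a one-sided test, and none of these is stated. The size of the gap depends on the assumptions set out above: it runs from about 18 points (62% against 80%) at the 20% end to about 3 points at the 30% end for the unmatched test, and it closes at the 30% end with a pair correlation of about 0.1.

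The effect is confined to the published justification for 424 participants; no planned analysis changes. I rate it minor to moderate: confident on the mismatch, less so on any single power figure.

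**What to change.** Keep 424 and rewrite the power sentence in one of three ways, stating sidedness and whether the calculation is matched:

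- **6-month window:** 212 per group gives 80% power for an odds ratio of about 1.95–2.17, at a 6-month background of 11–16% (two-sided, unmatched, constant hazard assumed).
- **12-month window:** 212 per group gives about 82–89% power for an odds ratio of 1.9 at a background of 20–30%, provided that rate is accepted as the 12-month risk in people already on treatment.
- **Keep the present claim:** state and justify either a 6-month background of at least about 18.5% or the pair correlation relied on.

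The cost is one sentence. No participants are added and no analysis changes. The first option makes the stated detectable effect less favourable.
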